## **7.2 Sample Size**

We conducted sample size calculations for change in depressive symptom severity. We powered our study to detect meaningful changes in depressive and anxiety symptoms. Using an alpha of .05 and power of .85, we will be able to detect a standardized effect size of 0.25 with a sample size of 578 individuals in total (289 per arm). We are assuming a retention rate of 88% (as per our previous study and experience in the current study) and power of 85% (per PCORI's request). A standardized effect size of 0.2 to 0.3 is widely considered to be a small effect size. We therefore plan to enroll 657 participants in the study, and, with a retention rate of 88%, we will have > 85% power to detect small effect sizes for these outcomes. Adjustment for covariates in multivariable analyses for numeric outcomes may make the residual SD smaller than the raw SD, improving precision and power.

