**Aim 1 Analyses:** We will compare changes in depressive (PHQ-9) and anxiety (GAD-7) symptom severity from baseline to three months postpartum and 3rd trimester. The multivariate analyses will follow an analytic plan similar to that of Aim 1, using linear mixed models to assess primary and secondary outcomes. We will conduct separate analyses comparing symptom exacerbation from baseline to 3rd trimester and baseline to 3 months postpartum. **Exploratory analyses (1a):** Previous work among pregnant women found rates of elevated depressive symptoms were 19.9% and 17.1% for Black and Latina women, respectively, compared to 9.5% of White women. We will explore the disparities in maternal mental health for Black and Latina women in our sample. Exploratory Aim 2a will follow the same analysis plan as 1a.

**Aim 2 Hypothesis:** Women assigned to Glow/GC will report more person-centered care (**1°**), respectful care (**2°**), and prenatal care satisfaction (**2°**) than women assigned to CPSP/IC, at 3 months postpartum (1° timepoint) and in the 3rd trimester (2° timepoint).

**Aim 2 Analyses:** We will use quantitative and qualitative methods to assess patient perceptions of person-centered care, respectful care, and satisfaction with care. The quantitative analysis will follow methods similar to those described in Aim 1, using linear mixed models for the PCPC and PCMC-US, MORi, and PCSS numeric outcomes. **Exploratory analyses (2a)** will follow the same plan above for the Black and Latina subgroups. **For Aim 2b**, in-depth interviews will focus on experiences of respectful and disrespectful care during the current pregnancy or in the past, experiences of racism in care or in other settings, and barriers/enablers of accessing care or services in their family/social network. The study will generate digital audio recordings and

transcripts encrypted when in transit. Data will be entered, coded, memoed, and organized using the Dedoose software program, which allows for open coding, theoretical memoing, and detailed conceptual matrixing of transcript and memo data within and across participants. Sorting functions allow for cross-group comparison by code or characteristic and for establishing a system of inter-coder reliability. We will store all data on a secure server at UCSF, accessible only to the investigative team via password-protected, encrypted computers.

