*Missing outcomes and covariates:* As baseline data will be collected at time of treatment assignment, and clinical outcomes will be obtained from medical record review, we do not estimate substantial missing data for Aim 3. We plan to reduce missing data for Aims 1 and 2 through our retention plan. We will record all reasons for study withdrawal and missing data. Participants lost-to-follow up will undergo medical record review for the outcomes of preterm birth and gestational age. Our mixed model analyses offer robust protection against data that are missing at random. We will assess missing data across study covariates and time points and use multiple imputation if it is appreciable. Pregnancies that end in miscarriage, abortion or fetal death prior to 20 weeks gestation will not be included in analysis.

*Heterogeneity of treatment effect (HTE):* We will assess if the effectiveness of Glow/GC compared with CPSP/IC differs by practice or patient characteristics through interaction analyses. Pre-specified analyses of treatment heterogeneity include: complications of pregnancy, parity, race/ethnicity, provider type (CNM, MD, NP). We will also conduct exploratory analyses on additional covariates (social support, site, size of practice or location, prior experiences of racism) to assess treatment differences. HTE will be assessed using interactions between

treatment assignment and each proposed effect modifier tested with a cut-point of ( $p < .10$ ) for HTE.

*Avoidance of bias:* The use of randomization of treatment initiation within practices allows us to minimize the risks of confounding and selection bias. More efficient designs with less susceptibility to bias are unfortunately not feasible in this study, as the treatment is administered at the practice level and needs to be incorporated without substantial interruption to clinical processes. To enhance generalizability of the study, we are recruiting from a diverse low-income patient population including English- and Spanish-speakers, with study staff and all assessment tools available in both languages. While we cannot mask treatment assignment to providers, participants or study staff, we will make every effort to ensure equivalent study procedures across both groups. Chart review and data analysis will be performed by study staff masked to treatment assignment to reduce ascertainment bias.

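### Aim 1 reads most naturally as change-score comparisons, one per follow-up; name the baseline score as a covariate and fit both follow-ups in one model

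*Combined protocol and SAP*

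**What the plan says.** Section 7.5 (Aim 1 Analyses) compares PHQ-9 and GAD-7 changes from baseline to each follow-up with linear mixed models, and then states: "We will conduct separate analyses comparing symptom exacerbation from baseline to 3rd trimester and baseline to 3 months postpartum". The model is not written out. The paragraph says it resembles the plan for Aim 1, which is itself. The change log in Section 10.0 shows that the aims were reordered, which probably explains the circular reference.

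On covariates, the opening of Section 7.5 promises adjustment for potential confounders without listing them. Section 7.2 expects covariates to reduce the residual SD but names none. Section 5.1.3 confirms that depression and anxiety are measured at baseline.

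On sizing, Section 7.2 says "We conducted sample size calculations for change in depressive symptom severity" and "Using an alpha of .05 and power of .85, we will be able to detect a standardized effect size of 0.25". It does not say which SD standardizes the effect.

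On missing data, Section 7.5 states: "Our mixed model analyses offer robust protection against data that are missing at random". It adds multiple imputation if missingness is appreciable, with no threshold and no imputation model.

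**The concern.** Two things are at stake on the primary endpoint.

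- **Precision.** A change score subtracts the whole baseline value, although only part of it predicts the follow-up score. Conditioning on baseline removes the excess variance and corrects for chance imbalance.
- **Missing data.** Section 7.2 expects 12% loss. Likelihood-based protection extends only to scores that are in the model. If the postpartum analysis contains only baseline and postpartum scores, a woman who worsened by the third trimester and then left is treated as though only her baseline were known. Participants know their arm (Section 7.4) and the programs differ in contact (Sections 4.1 and 4.2), so dropout that differs by arm cannot be ruled out.

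**Working it through.** **1. The plan's own figure.** Inputs from Section 7.2: alpha 0.05, power 0.85, effect 0.25, retention 88%.

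- n per arm = 2(1.960 + 1.036)² / 0.25² = 287.3, so 288 by the normal formula. The noncentral t gives 289, as stated.
- Power at 289 per arm is 0.852 (normal) or 0.851 (t).
- 578 / 0.88 = 656.8, so 657, as stated.
- A one-sided test would need only 231 per arm, so the calculation is two-sided.

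The sizing is therefore an unadjusted two-sample comparison and takes no credit for baseline adjustment.

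**2. Gain from conditioning on baseline.** Assume SD σ at both times and correlation r (not given in the plan).

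- Variance of change: 2σ²(1 − r).
- Residual variance given baseline: σ²(1 − r²).
- Ratio: (1 + r)/2.

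Power is Φ(d√(289/2) − 1.96). Case A takes 0.25 in SD-of-change units, so adjusted d = 0.25/√((1 + r)/2). Case B takes it in raw-SD units, so d = 0.25/√(2(1 − r)) for change and 0.25/√(1 − r²) adjusted.

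| r | Variance ratio | A: change | A: adjusted | B: change | B: adjusted |
|---|---|---|---|---|---|
| 0.3 | 0.65 | 0.852 | 0.961 | 0.719 | 0.883 |
| 0.4 | 0.70 | 0.852 | 0.949 | 0.783 | 0.906 |
| 0.5 | 0.75 | 0.852 | 0.935 | 0.852 | 0.935 |
| 0.6 | 0.80 | 0.852 | 0.919 | 0.919 | 0.964 |
| 0.7 | 0.85 | 0.852 | 0.903 | 0.973 | 0.988 |

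**3. Where the gain comes from.** A simulation used 3,000 replicates, 329 per arm, equal correlations among the three times, 88% retention completely at random, and r from 0.4 to 0.6. Power was:

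- 0.84-0.86 for change scores
- 0.85-0.87 for an unconstrained two-time-point mixed model
- 0.92-0.94 for postpartum adjusted for baseline
- 0.92-0.94 for both follow-ups modelled jointly given baseline

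Adding the third-trimester score raises effective sample size by only 1.0-1.7%. Nearly all the gain is baseline adjustment.

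**4. Missing-at-random check.** Same set-up, with dropout depending on the third-trimester score. Bias is shown as a percentage of the effect.

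| Dependence | Two-time-point mixed model | Baseline-adjusted postpartum only | Joint model |
|---|---|---|---|
| Alike in both arms | 1.2 to 2.1 | 1.1 to 1.8 | −0.7 to 0.0 |
| Opposite by arm | 20.7 to 24.8 | 21.0 to 24.9 | −0.6 to 0.4 |

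Complete-case change scores were also close to unbiased (within 1%). That happens only because the equal correlations make the third-trimester score relate identically to baseline and postpartum.

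**5. Reliance on equal baselines.** Suppose the arms truly differ by δ at baseline and trends are parallel. The change score is then unbiased. The baseline-adjusted estimate is (effect + δ) − rδ, so it is off by (1 − r)δ. A model that constrains the baseline means to be equal is off by the same amount. At r = 0.5 and δ = 0.1 SD this is 0.05 SD, or 20% of a 0.25 SD effect.

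Provider, practice and group clustering is left out throughout, as in Section 7.2.

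**The case against.** **The reading is not certain.** Section 7.5 names linear mixed models before it mentions separate analyses, and that sentence may mean separate contrasts or an additional look at worsening. Section 7.1.1 also lists change from third trimester to postpartum, which the two separate analyses do not produce but a joint model does. This stands: change scores by time point is the likeliest reading, not the only one.

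**Baseline adjustment may be intended.** The confounders are unnamed, baseline scores are collected, and Section 7.2 anticipates a gain from covariates. This also stands. If baseline PHQ-9 is on the list, almost all of the power gain is already in the plan.

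**Multiple imputation could supply the protection.** It could, if the imputation model includes the third-trimester score. The plan states neither that nor when imputation would be used, so this answers the point only in part.

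**Two stronger readings are tempting.**

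- A reader might infer that a model forcing equal baseline means is free. The documents do not support this. Women are placed by provider and due date, and those arriving after a Glow cohort reaches 12 go to CPSP (Section 2.3), so equal baselines are not guaranteed. Step 5 gives the price.
- A reader might infer that the gain pays for the clustering that Section 7.2 omits. That depends on figures the plan does not give. Assume Glow groups of 9 and an ICC of 0.05. The design effect is 1 + 8 × 0.05 = 1.4 in Glow and 1 in CPSP, an average of 1.2. Case A power is then 90.5%, 88.5% and 86.5% at r = 0.4, 0.5 and 0.6, but 84.4% at 0.7. Groups form after baseline, so their shared variance need not shrink with adjustment. Held fixed, it gives 88.5%, 86.8%, 85.1% and 83.3%. Provider and practice effects would come on top.

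**Conclusion.** The point holds as a recommendation for a better-specified primary analysis. On the likeliest reading, the plan gives up about 7 to 10 points of power at r = 0.6 to 0.4 in Case A. Baseline adjustment is also better in Case B at every correlation from 0.3 to 0.7. The size rests on an assumed correlation and an assumed unit for the 0.25, and it disappears if baseline PHQ-9 was already an intended covariate.

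The missing-data gain is separate. It is small if dropout follows the third-trimester score alike in both arms, and material only if the dependence differs by arm. Nothing in the documents shows that it will. The claim of missing-at-random protection nevertheless needs the third-trimester score in the model. Adding baseline as a covariate to a postpartum-only analysis does not supply it.

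**What to change.** For PHQ-9, and likewise for GAD-7, specify one linear mixed model:

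- **Outcomes:** third-trimester and 3-month postpartum scores.
- **Fixed effects:** the baseline score, named as a covariate, with baseline-by-time and arm-by-time terms.
- **Covariance:** unstructured within woman, plus practice and provider effects.
- **Estimates:** the arm difference at 3 months postpartum is primary. The third-trimester difference comes from the same fit. Replace symptom exacerbation by mean difference.
- **Women who deliver before the third-trimester interview** (Section 5.1.4): keep them in the model through their postpartum score.
- **Sensitivity analyses:** an unadjusted change-score comparison, which does not rely on equal baseline means, or a baseline-constrained three-time-point model. The SAP should say that the constraint assumes equal baseline means, which this allocation does not guarantee.

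Remove the circular reference to Aim 1. If multiple imputation stays as a fallback, state its trigger and include the third-trimester score in the imputation model. The change is to SAP wording. It uses data already planned, needs no more participants, and adds slightly more analysis work.

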## **8.0 HUMAN SUBJECTS CONSIDERATIONS**

### **8.1 Ethical Review**

All study procedures, consent forms, study questionnaires and recruitment materials were reviewed and approved by the CSU Fresno and UCSF Institutional Review Boards (IRB). Any subsequent modifications to study procedures or documents after initial approval will be submitted for review and approval. Review will be with respect to scientific content and compliance with applicable research and human subjects regulations.

IRB review of the study protocol will occur at least annually. Study staff at CSU Fresno and UCSF will provide safety and progress reports to the IRBs at least annually and within three months of study termination or completion. These reports will include the total number of participants enrolled in the study, the number of participants who completed the study, all changes in the research activity, and all unanticipated problems involving risks to human subjects or others.

### **8.2 Informed Consent**

Written informed consent will be obtained from each study participant prior to enrollment using a consent form approved by the local IRB in accordance with all applicable regulations. A copy of the study informed consent form will be offered to the participant at enrollment (Appendices 3 and 4).

### **8.3 HIPAA**

Permission for release of medical records for ascertainment of clinical endpoints will be obtained from participants with the Health Insurance Portability and Accountability (HIPAA) research authorization form, which documents the personal health information that may be released, to whom it may be released, how it may be used, when permission for its release expires, and under what terms permission may be cancelled (Appendices 5 and 6).

### **8.4 Risks**

This is a minimal risk research study commensurate with what might be expected in standard prenatal care. However, some interview questions are sensitive in nature and participants may feel uncomfortable answering. For example, the PHQ-9 scale includes measures of severity of depressive symptoms.

Risk will be minimized as follows. First, all participants will be informed, prior to participation, that they are free to terminate their participation at any time or to decline to answer any questions or participate in any part of the study. During the consent process, we will ensure that the participant understands this principle and feels free to exercise this option at any time. Second, study

questionnaires will be administered by RRSs in a private area and participants will be advised that they are free to skip any question they are uncomfortable answering. Finally, the RRS will enter participant responses directly in REDCap which will be programmed to alert the RRS to scores > 0 on item 9 of PHQ-9 (i.e., endorses “thoughts that you would be better off dead, or thoughts of hurting yourself in some way”) and prompt the RRS to follow the study protocol.

If a study participant scores > 0 on item 9 of PHQ-9, the recruiter will ask the participant if she has received any counseling or help regarding those feelings. If the participant responds affirmatively, the recruiter will encourage her to contact this person. The RRS will refer the participant to Perinatal Wellness Center and urge her to call the Central Valley Suicide Prevention Hotline. Additionally, all women with scores > 0 on item 9 of PHQ-9 will be asked to consider contacting their prenatal care provider. Periodic screening for depression is now standard practice in prenatal care.

If RRSs have questions or concerns, they can contact [name], PhD, a study co-investigator and licensed psychologist with expertise in perinatal mental health, at [contact] to review the situation.

## **8.5 Benefits**

There are no direct benefits to study participants. However, some participants enjoy contributing to scientific knowledge about prenatal care. Additionally, women assigned to Glow/IC may enjoy talking with other pregnant women while attending group prenatal care sessions.

The study will help low-income pregnant people and their providers determine which approach to enhanced prenatal care is most effective in reducing the risk of preterm birth, lowering symptoms of depression and anxiety, and providing care that feels satisfying and respectful. Furthermore, if shown to be effective, the study will generate evidence for policy makers and payers to expand access to enhanced group prenatal care for low-income women.

## **8.6 Incentives**

Participants will be compensated for their time and effort in this study through remuneration of \$30 for the baseline questionnaire and \$50 for the third trimester and postpartum questionnaires.

Participants will also be sent reminder cards for questionnaires and a baby beanie with a card when their child is born.

## **8.7 Confidentiality**

Confidentiality will be maintained by administering study questionnaires in a private area and asking participants how they wish to be communicated with. Participant study information will not be released without the written permission of the participant except as necessary for monitoring by the NIH and/or the site IRB.

# **9.0 ADMINISTRATIVE PROCEDURES**

## **9.1 Study Coordination**

Study implementation will be directed by this study protocol. Protocols for training and study team communication are covered in sections 9.1.1. and 9.1.2. Section 9.1.3 reviews database management and data quality monitoring plans. Use of information is described in Section 9.2.

### **9.1.1 Trainings**

The site director, project manager, and the RRC at CVHPI will train all recruitment team members. Topics covered may include:

- Research ethics and confidentiality
- CITI and HIPAA trainings
- Study background, justification and aims
- Inclusion and exclusion criteria, eligibility screening
- In-person and remote interview scheduling
- Approaching and contacting potentially eligible participants
- Etiquette for in-person approach in the clinic waiting area
- Etiquette for remote approaches by phone
- Documenting approaches
- Informed consent (remote and in-person)
- Comparator assignment protocol
- Questionnaire administration (in-person and remote)
- Baseline questionnaire
- Third trimester questionnaire
- Postpartum questionnaire
- Qualitative interview training
- Equipment
- Tablets
- Laptops
- Zoom scheduling and recording
- Remuneration
- Tracking of cash payments
- Tracking of remote payments
- Retention
- Withdrawal and discontinuation
- Health literacy and the social determinants of health
- Diversity and inclusion

The data manager at UCSF will train all project staff on topics related to database entry with REDCap and will monitor data quality. This may include:

- Forms for following study participants and scheduling subsequent interviews
- Approach, screening, contact, and consent forms
- Baseline, third trimester, and postpartum forms
- Stillbirth or Infant death forms
- Entering data for participants who are lost to follow up, had pregnancy losses prior to 20 weeks, and participant withdrawals or discontinuations
- Using weekly data quality reports to monitor enrollment and completion of study questionnaires
- Creating reports and data visualizations for study staff

### **9.1.2 Study Communication**

Calls and in-person meetings will be scheduled throughout the study period and on an as-needed basis to ensure clear communication, collegial collaboration, and rapid response to any challenges that may arise.

#### Investigator Calls

The PI will lead monthly conference calls with study staff. Topics to be discussed may include:

- Project timelines
- Site recruitment plans
- Enrollment and retention reports
- Study design and implementation
- Questionnaire revisions (as necessary)
- Data analysis plans, progress and results
- Manuscript and abstract plans and progress
- Review of draft manuscripts and abstracts
- IRB renewals and modifications
- Budgets and contracts
- Other study management issues as needed

#### Research Coordinator Meetings

The RRC at CVHPI will hold daily meetings with the RRSs, and the project manager, at a minimum, will attend weekly with the site director participating as needed. Any new project manager should participate daily in these calls for at least one month. Coordinator meetings will cover topics including:

- Current totals for approached, scheduled for enrollment, enrolled, scheduled for interviews, followed-up, consents completed, and status uploading to REDCap, by each site
- Successes, challenges, and new ideas for:
  - Screening and approaching patients
  - Reaching recruitment targets
  - Utilizing technology (tablets, printers, Wi-Fi)
  - Administering questionnaires and qualitative interviews
  - Scheduling and coordinating follow-up interviews
  - Any issues needing attention at the medical provider level
  - Other issues as needed

## **9.2 Database Management and Data Quality Monitoring**

Comparator assignment, survey responses, and medical record abstraction data for all sites will be collected and stored in REDCap databases hosted centrally at UCSF. Data will be maintained behind an institutional firewall and accessible through a web portal via login credentials known only to qualified study staff. Comparator assignment will be masked to RRSs during data collection with the exception of the one bilingual RRS on staff. RRSs can maintain their own tracking and recruitment logs for each site as long as the final forms are entered into the local REDCap database. Protected health information, such as patient names, medical record number, estimated due date, date of birth, telephone number, mailing address, and email address will be de-identified after enrollment to all other study staff. A unique study identifier will be generated for each participant to link records within the database.

Data from REDCap will be used to develop monthly recruitment and enrollment reports. Study data will be transferred to statistical software for cleaning, reporting and analysis. Data will be exported from REDCap to perform data visualizations for study team meetings.

